### Intervention

#### Facility-based care

FBC will be available to all participants in this trial. Facility-based care is the care usually provided by mental health practitioners for persons with schizophrenia and their families. No guidelines or protocols are available for FBC as this is more representative of usual care in China. Psychiatrists from general or psychiatric hospitals prescribed antipsychotic medications and provide consultation, including specific information about the illness, encouragement on adherence and discussion about other specific concerns. The frequency of FBC was once per month or more, which will be determined by clinical need.

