### Outcome assessment

For the primary outcome assessments, we will record the following indicators as intermediate outcome for each participant at baseline, intermediate (6 months after initiating intervention) and endline (12 months after initiating intervention) survey:

Symptoms of schizophrenia will be measured using the Positive and Negative Syndrome Scale (PANSS) [13].Personal and social function will be measured by Personal and Social Performance Scale (PSP) [14, 15].Antipsychotic adherence will be assessed using Medication Adherence Rating Scale (MARS) [16].Knowledge of illness will be measured using the Knowledge About Schizophrenia Test (KAST) [17] for each participant and their caregiver.Hospital readmission records will be extracted from electronic medical records using participants’ national identification number.

We will also be assessed the following indicators as long-term outcome for each participant at baseline and endline (12 months after initiating intervention) survey:

Physical function will be measured using Activity of Daily Living Scale (ADL) and Instrumental Activity of Daily Living Scale (IADL).Social support of participants will be measured using Perceived Social Support Scale (PSSS) [18].Quality of life of participants will be assessed using the EuroQoL five-dimensional instrument (EQ-5D) and the Schizophrenia Quality of Life Scale (SQLS) [19].The family burden of caring will be measured through participants’ caregiver interview using Burden Assessment Scale for families of the seriously mentally ill (BAS) [20].

For the secondary outcome assessment, we will calculate the cost of schizophrenia by combining the self-reported cost from participants or their caregivers and the electronic medical records. The direct cost includes inpatient during the last year and outpatient cost during the last month, which will be extracted from the electronic medical records, and self-medication cost reported by participants or their caregivers. The indirect cost includes loss of wages of caregiver, fees of transportation, accommodation and meals due to accompanying and care, and other cost during the inpatient and outpatient service utilization. All the indirect costs were self-reported by participants or their caregivers. The secondary outcome will be assessed at baseline, intermediate and endline survey. Table 2 describe the details of each outcome measure in this study.

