#### Cost-effectiveness analysis

Direct costs of the CBR intervention will be estimated by deriving a monetary value based on actual cost. Cost of illness, as the secondary outcome will be computed based on electronic medical records & self-reported data, and then compared at intermediate line and endline. Cost-effectiveness will be assessed by calculating the incremental cost-effectiveness ratios, which will show the extra cost incurred to produce a unit improvement in symptoms, personal and social function, as well as QALYs gained at the endline. To explore the uncertainty around the estimates, cost-effectiveness acceptability curves will be derived to provide the probability of advantages for the FBC combined CBR at a range of ‘willingness to pay’ threshold levels.

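### Direct cost pairs a 12-month inpatient window with a 1-month outpatient window, so its outpatient part does not span the endline ICER horizon, and the month-6 inpatient window is half pre-intervention

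*Protocol article*

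**What the plan says.** Cost of illness is the only outcome that the protocol article labels secondary (Table 2), and cost-effectiveness is the second of the trial's two overall objectives (Objectives). The Outcome assessment section sets the windows for direct cost: "The direct cost includes inpatient during the last year and outpatient cost during the last month". It also names the source: "which will be extracted from the electronic medical records, and self-medication cost reported by participants or their caregivers". On timing it says: "The secondary outcome will be assessed at baseline, intermediate and endline survey". The follow-up surveys are placed at "intermediate (6 months after initiating intervention) and endline (12 months after initiating intervention) survey".

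The Cost-effectiveness analysis section says that cost of illness "will be computed based on electronic medical records & self-reported data, and then compared at intermediate line and endline". The ICERs are to show "the extra cost incurred to produce a unit improvement in symptoms, personal and social function, as well as QALYs gained at the endline". The intervention itself is costed separately, at its actual cost.

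One pair of look-back windows is given for all three surveys. The article states no separate window for month 6, no scaling of the outpatient month, and no rule for combining the month-6 and month-12 costs. On usual care, the Facility-based care section says: "The frequency of FBC was once per month or more, which will be determined by clinical need".

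**The concern.** The endline ICER needs the cost incurred over the 12 months of follow-up. Inpatient cost and the cost of community-based rehabilitation (CBR) can be counted for that whole period, but outpatient cost is collected for one month only. Usual care brings outpatient contact at least monthly, and participants must be stable and living in the community. Outpatient cost can therefore arise in every month, and most of those months would go unobserved. An analysis rule written later cannot recover months that were never extracted.

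The month-6 survey has a different problem. A one-year look-back at that point reaches six months behind the start of the intervention, so the planned month-6 comparison mixes cost that the intervention could affect with cost that it could not.

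At stake are the secondary outcome and the numerator of the ICER, which serve the second objective.

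**Working it through.** The article gives no cost figure, variance or incremental cost, so there is no stated result to reproduce. The check is interval arithmetic on the stated windows, followed by assumed monthly profiles.

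**Inputs.** Inpatient look-back of 12 months, outpatient look-back of 1 month, and surveys at months 0, 6 and 12 (all from Outcome assessment). Month 0 is the start of the intervention. Sessions: 12 in the first six months and 6 in the last six (CBR delivery), which is 2 per month and then 1 per month.

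**Step 1: what each window covers.** A window of length L at survey time t covers t - L to t.

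| Survey | Inpatient window | Pre-intervention months | Follow-up months | Outpatient window |
|---|---|---|---|---|
| Month 0 | -12 to 0 | 12 | 0 | -1 to 0 |
| Month 6 | -6 to 6 | 6 | 6 | 5 to 6 |
| Month 12 | 0 to 12 | 0 | 12 | 11 to 12 |

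Outpatient coverage of follow-up is 1/12 = 8.3% at endline, or 2/12 = 16.7% with month 6 added. So 11 or 10 of the 12 months are unobserved. Inpatient coverage at endline is 12/12.

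**Step 2: can scaling repair the outpatient part?** Let d(m) be the arm difference in outpatient cost in month m, and T the sum of d(1) to d(12). The share of T recovered is 12 x d(12) / T if the endline month is scaled to a year, and 6 x [d(6) + d(12)] / T if each observed month stands for its half-year. The profiles below are assumptions, chosen to show the range.

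| Assumed profile of d(m) | Endline month x 12 | Both months x 6 |
|---|---|---|
| Level | 1.00 | 1.00 |
| Halved in months 7-12 | 0.67 | 1.00 |
| Months 1-6 only | 0 | 1.00 |
| Months 7-12 only | 2.00 | 1.00 |
| Linear rise, m/12 | 1.85 | 1.38 |
| Linear fade, (13 - m)/12 | 0.15 | 0.62 |

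Worked example, halved profile: T = 6 x 1 + 6 x 0.5 = 9, and 12 x 0.5 / 9 = 0.67. Using both months copes with a step at month 6 but not with a trend inside the half-years. With no scaling, the endline month holds 8.3% of a level difference, and 0% to 17% over these profiles.

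**Step 3: the month-6 inpatient comparison.** Let control cost be level at C per month, and let the intervention cut it by a fraction r from month 0.
- Control total over -6 to 6: 12C. Intervention total: 6C + 6C(1 - r) = 12C - 6Cr.
- Absolute difference: 6Cr, the same as in a 0-6 window.
- Relative reduction seen: 6Cr / 12C = r/2, so a true 20% appears as 10%.
- Variance relative to a 0-6 window, with equal variances in the two half-years and correlation rho between them: 2 + 2 x rho. This is 2 at rho = 0 and 3 at rho = 0.5.

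**The case against.** The strongest defence is that sampling one outpatient month and scaling it up is unbiased when cost is level, and that monthly usual care makes one month a natural cycle. The scaling rule may well stand in a full protocol or analysis plan that is not shown, and its absence from the article is no fault. This stands as far as it goes: 8.3% is a coverage figure, not a measure of error. But scaling rests on a level arm difference, and the fall from two sessions to one per month gives reason to doubt that. It is a reason for doubt, not evidence of any particular profile.

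Three stronger readings are tempting, and the documents do not support them.
- A reader might infer that every look-back reaches improperly into pre-trial time. The baseline window is meant to be pre-trial, and the month-12 inpatient window matches follow-up exactly. Only the month-6 inpatient window is affected.
- A reader might infer that months 0-6 of inpatient cost are counted twice. The article describes a comparison at each of the two surveys and nowhere adds the two costs together.
- A reader might infer that the incremental cost is simply wrong. The endline inpatient component and the separately costed intervention are sound, and the month-6 absolute difference is noisier rather than biased under randomisation.

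It is also fair to say that the article does not describe how complete or accessible the outpatient records are. The fix assumes that they can be extracted for the whole follow-up.

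**Conclusion.** The concern holds in two limited parts.

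First, the outpatient component of direct cost does not match the inpatient window or the 12-month ICER horizon, and it leaves 10 or 11 of 12 follow-up months unobserved. Scaling the endline month recovers between 0 and 2.0 times the true difference over the assumed profiles, and scaling both observed months recovers 0.62 to 1.38 times. Both recover it exactly if the difference is level.

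Second, the planned month-6 cost comparison draws half of its inpatient window from before the intervention. A relative effect is roughly halved if monthly cost is level, and the variance is about 2 to 3 times that of a 0-6 window, assuming equal variances and a correlation of 0 to 0.5 between half-years. The absolute difference keeps its expectation.

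Both parts take the stated windows to apply at every survey, as the article is written. They bear on the secondary cost outcome, and the first part also bears on the ICER. The primary PANSS analysis is not affected. The change is worth making because it is cheap and the months lost cannot be restored by later analysis.

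**What to change.** Extract inpatient and outpatient costs from the electronic medical records for the same non-overlapping windows in both arms: a pre-baseline period, months 0-6 and months 7-12. Use months 0-6 for the month-6 comparison, and sum the two follow-up windows for the endline ICER. Each follow-up month is then counted once for both cost types, and no scaling is needed.

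The cost is a longer date range for outpatient records in an extraction that is already planned, assuming those records are available for the whole follow-up. Leave the recall period for self-reported items (self-medication, caregiver wages, travel, meals) as it is: lengthening it would trade a coverage gap for recall error, and the article states no window for these items that could be shown to be wrong.

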**Primary outcome**					
* Intermediate outcome*					
Symptoms of schizophrenia	Participants	Positive and Negative Syndrome Scale (PANSS)	√	√	√
Personal and social function	Participants	Personal and Social Performance Scale (PSP)	√	√	√
Antipsychotic adherence	Participants	Medication Adherence Rating Scale (MARS)	√	√	√
Knowledge of illness	Participants & primary caregiver	the Knowledge About Schizophrenia Test (KAST)	√	√	√
Hospital readmission	Participants	Electronic medical records	√	√	√
* Long-term outcomes*					
Physical function	Participants	Activity of Daily Living Scale (ADL) & Instrumental Activity of Daily Living Scale (IADL)	√		√
Social support	Participants	Perceived Social Support Scale (PSSS)	√		√
Quality of life	Participants	the EuroQoL five-dimensional instrument (EQ-5D) & the Schizophrenia Quality of Life Scale (SQLS)	√		√
The family burden of caring	Primary caregiver	Burden Assessment Scale for families of the seriously mentally ill (BAS)	√		√
**Secondary outcome** Cost of illness	Participants/ Primary caregivers	Electronic medical records & self-reported self-medication cost, loss of wages of caregiver, fees of transportation, accommodation, and meals due to accompanying and care and other cost during the inpatient and outpatient service utilization	√	√	√

### Quality assurance and fidelity management

To ensure that the CBR intervention is of adequate fidelity, each district will be assigned a coordinator to monitor the delivery of CBR sessions in the three sub-districts from intervention arm every month. The intervention coordinators will record and rate the key contents of the CBR sessions such as interactions between CBR workers and participants, the ways of module presentation, etc., according to a specially designed rating scale. Regular meetings will be held to provide feedback for improving the delivery of the intervention to all CBR workers to maintain quality benchmarks of the trial. Any significant divergence from the intervention manual will lead to suitable corrective action to harmonize the intervention across the sites.

To ensure the adequate quality of outcome measurements in the baseline, intermediate and endline survey, three procedures of supervision will be implemented. First, all the interviews, including both the part of primary care physicians and will be sound recorded (after obtaining the consent of participants), the records will be directly sent to team researchers and experts in psychiatry (for symptoms and function assessment) every day for quality control purpose. Any divergence from the protocol norms will lead to communication with data collectors for correction, and significant errors will lead to re-interview for outcome measurements. Second, each district will be assigned a coordinator to monitor 20% interviews of every sub-district through randomly onsite visits. The coordinator will provide feedback based on a specially designed assessment form to the team researchers. Third, researchers will also conduct casual inspection to check the quality of 10% of the finished questionnaire and assessment through the online platform. The submitted questionnaire will be sent back to data collector for re-check if any illogical error was found. A weekly group meeting with data collectors, researchers and experts in psychiatry will be held to ensure the interview norms and to achieve the overall quality benchmarks.

### Statistical issue

#### Sample size estimation

Based on the data from the earlier random controlled trials [9, 21], it was assumed that the participants in the intervention arm will have 20% reduction on the PANSS total score mean reduction after the 12-months CBR, and there was no change observed for participants in the control arm. The intra-class correlation within the three districts was set at 0.05 and alpha was set as 0.05. Based on methods from previous literature [22], a sample size of 110 participants in both intervention arm control arm was calculated for this trial, which will give us 90% power to detect the difference. The required sample size of 220 was increased to 264 to allow for 20% attrition. The total number of participants will be divided slightly unequally between sub-districts for reasons of feasibility.

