**Methods:**

This trial is a cluster randomized controlled trial design in China. The trial will be conducted at three districts of Weifang city, Shandong province. Eligible participants will be identified from the psychiatric management system where community-dwelling patients with schizophrenia have been registered. Participants will be recruited after providing informed consent. 18 sub-districts will be randomly allocated in a 1:1 ratio to facility-based care (FBC) plus CBR (intervention arm) or FBC alone (control arm). The structured CBR intervention will be delivered by trained psychiatric nurses or community health workers. We aim to recruit 264 participants. The primary outcomes include symptoms of schizophrenia, personal and social function, quality of life, family burden of caring, etc. The study will be conducted according to good ethical practice, data analysis and reporting guidelines.

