## Methods

### Study design

The design is a cluster randomized controlled trial with sub-district as the unit of randomization. There are mainly three reasons for choosing cluster randomization as the method of randomization: (1) CBR was provided as group intervention at community healthcare, which exclude the possibility of randomization at individual level; (2) randomization at sub-district will be more economical and less time-consuming for both provider and participants; (3) The acceptability will be maximized, and the possibility of contamination could be minimized if all participants in a sub-district are allocated to either intervention or control arms. The study flow chart is presented in Fig. 1. Eighteen sub-districts from three district in Weifang, Shandong province were included for the trial, 9 will be randomly allocated to the intervention arm (FBC plus CBR) and 9 randomly allocated to the control arm (FBC alone). In total, 334 participant dyads (patients and their caregivers) will be recruited, with 18.6 participant dyads on average recruited for each sub-district.

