### Setting

The trial will take place in Hanting, Kuiwen and Weicheng district, Weifang city, Shandong province in China. The three districts have a population of 1,470,000 persons in 23 sub-districts. Six sub-districts in each district were chosen, yielding to 18 sub-districts in the trial. There is a community health center in each sub-district that covering the facility-based care of local people with severe psychiatric disorders including schizophrenia. The number of registered schizophrenia patients of each sub-district ranges from 52 to 138, with 12 to 25 patients are planned to recruit.

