### Participant flow

#### Participant identification

In China, most of the community-dwelling patients with schizophrenia who have been diagnosed in hospitals or primary care services are registered in the National Information System for Psychosis of China. The recruitment processes of this trial are as follows: Primary care physicians from 18 sub-districts of Hanting, Kuiwen and Weicheng districts, identify the potential participants who met the inclusion criteria from their local registered community-dwelling patients with schizophrenia. Eligible patients will be invited to join the trial by primary care physicians or nurses. They will be given information about the trial and the study procedure in a way appropriate to the participants’ literacy level by telephone or face-to face. Those who consent (or, for those without decision-making capacity, the caregiver will consent on their behalf) to participate will go to community health care center to sign the informed consent and complete baseline data collection. Within each sub-district, the recruitment will continue until approximately 20% of community-dwelling patients have been recruited.

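### The recruitment target is given as both 264 and 334 with no reconciliation, and 264 does not cover the 20% attrition it is said to allow for (220/0.80 = 275).

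*Protocol article*

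**What the plan says.** The Sample size estimation section of the protocol article sets the analysable requirement: "a sample size of 110 participants in both intervention arm control arm was calculated for this trial". The stated power of 90% is attached to that number. The attrition step follows: "The required sample size of 220 was increased to 264 to allow for 20% attrition". The Methods paragraph of the abstract repeats the inflated total: "We aim to recruit 264 participants".

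The Study design section gives another total: "In total, 334 participant dyads (patients and their caregivers) will be recruited, with 18.6 participant dyads on average recruited for each sub-district".

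Three further statements bear on how many patients will be enrolled:
- Setting: registers of 52 to 138 patients per sub-district, "with 12 to 25 patients are planned to recruit".
- Participant identification: within each sub-district, "the recruitment will continue until approximately 20% of community-dwelling patients have been recruited".
- CBR delivery: one group of 10 to 20 patients in each sub-district that receives the intervention.

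**The concern.** The total to be enrolled is a core design commitment. Completion, early closure and over-recruitment are all judged against it. Two totals 70 patients apart (70/264 = 27%) stand in the same article, so a final enrolment anywhere from 264 to 334 could be called on target or off target.

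Separately, the derivation of 264 does not do what the text says. An allowance for 20% attrition should leave the required number once 20% of those enrolled are lost. Raising 220 by 20% does not achieve that. If recruitment stopped at 264 and the planned attrition occurred, the trial would finish below its own requirement.

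**Working it through.** **Inputs.** From Sample size estimation: 220 required (110 per arm), 90% power, alpha 0.05 (sidedness not stated), ICC 0.05, attrition 20%, inflated total 264. From Study design: 334 dyads, 18.6 per sub-district, 18 sub-districts. From Setting: 12 to 25 per sub-district, registers of 52 to 138. From CBR delivery: groups of 10 to 20.

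**1. Reproducing the stated 264.** n × (1 + d) = 220 × 1.20 = 264. This matches exactly, so the total was obtained by multiplying by 1.2.

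**2. Does 264 allow for 20% attrition?**
- Completers: 264 × 0.80 = 211.2, about 9 below 220.
- Attrition that 264 can absorb: 1 − 220/264 = 16.7%.
- Correct inflation: n/(1 − d) = 220/0.80 = 275. By arm, 110/0.80 = 137.5, rounded up to 138, gives 276 in total.

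**3. Are 264 and 334 the same target in different units?** No. Each dyad contains one patient, so 334 dyads are 334 patients. If 264 instead counted both members of each dyad, it would be 132 dyads, which is further from 334.
- 334/18 = 18.56, which agrees with the stated 18.6, so 334 is not a typing slip.
- 264/18 = 14.67, which does not agree with 18.6.
- 334 does not follow from 220 with 20% attrition by either method (264 or 275). It would absorb 1 − 220/334 = 34.1%.

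**4. Effect on power.** No PANSS standard deviation or baseline mean is given, so 220 cannot be re-derived. It is taken as stated, and the effect size that gives 90% power at 220 is back-solved with two-sided alpha 0.05 and a normal approximation.
- Without clustering: d = (1.960 + 1.282) × √(2/110) = 0.437.
- With clustering by sub-district: m = 220/18 = 12.2; design effect = 1 + (12.2 − 1) × 0.05 = 1.56; d = (1.960 + 1.282) × √(4 × 1.56/220) = 0.546.

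Power is then Φ(d/√(4 × DE/N) − 1.960), where N is the number completing and DE is recomputed at m = N/18 (DE = 1 without clustering):

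| Enrolled | Completing at 20% loss | Power, no clustering | Power, ICC 0.05, 18 clusters |
|---|---|---|---|
| 264 | 211.2 | 88.8% | 89.3% |
| 275 | 220 | 90.0% | 90.0% |
| 334 | 267.2 | 94.7% | 92.9% |

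**5. Do the other recruitment statements settle which total applies?**
- 12 to 25 per sub-district: both 14.7 and 18.6 lie inside. Over 18 sub-districts the range spans 216 to 450.
- 20% rule: the average register needed is 14.67/0.20 = 73 for 264 and 18.56/0.20 = 93 for 334. Both lie within 52 to 138, and no mean is given. The rule does not match the 12 to 25 range at its ends either: 20% of 52 is 10.4 and 20% of 138 is 27.6.
- Groups of 10 to 20: 14.7 sits mid-range, 18.6 is near the ceiling, and the planned maximum of 25 exceeds it.

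**The case against.** The strongest reply is that little is at stake. The 90% power is attached to 220 analysable patients, not to either enrolment total, so the contradiction leaves that statement untouched. If 334 is operative, about 267 patients complete and the attrition slip has no consequence. If 264 is operative, the slip costs about one point of power. The power figures for 264 and 334 also rest on a back-solved effect, and the clustered ones on treating the ICC as a sub-district quantity, whereas the article describes it as within the three districts. All of this stands, and it limits the severity. It does not remove the contradiction or make 264 a correct allowance.

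A reader might infer two stronger conclusions.

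- *The trial is underpowered.* The documents do not support this. One of the two stated totals exceeds the requirement comfortably, and the other misses it narrowly.
- *334 is the true target and 264 should be deleted.* The 18.6 average shows that 334 is deliberate, and the midpoint of the register range (95, of which 20% is 19) points loosely the same way. But a midpoint is not a mean, and the 12 to 25 range fits both totals. An average register of about 93 is obtained only by working back from 334, so it is no independent support. The group size of 10 to 20 sits more easily with 14.7. In addition, 264 has a stated derivation, though a flawed one, while 334 has none. The article does not show which total is operative, and the choice is the sponsor's.

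This is not a matter of detail left to a fuller protocol or an analysis plan, because both totals and the attrition step are stated in the article.

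**Conclusion.** The point holds in two parts. First, the recruitment target is stated inconsistently, as 264 in the abstract and sample size section and as 334 patients in the study design section, a difference of 70 that nothing reconciles. This needs no assumption. Second, 264 does not allow for 20% attrition: it leaves about 211 completers against 220 and covers 16.7% loss, and 275 (276 with equal arms) is needed. This rests only on reading 220 as the number required after attrition, which is how the article presents it.

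The consequence for power is small and conditional: about 89% instead of 90% if 264 is operative, and no shortfall if 334 is. Those figures assume that 220 does give 90% power and that alpha is two-sided; the validity of 220 itself was not tested. Severity is moderate: the stated sample size is wrong and contradictory, with little effect on power.

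**What to change.** 1. In Sample size estimation, replace 264 as the attrition-adjusted minimum with 220/(1 − 0.20) = 275, or 276 (138 per arm) with equal arms.
2. State one operative target in the abstract, Study design and Sample size estimation. Either keep 334 and give the reason for exceeding the minimum, or drop it together with the 18.6 average.
3. For the chosen target, give the expected number completing at 20% attrition and the corresponding power.
4. Reconcile that target with the 20% recruitment rule (Participant identification), the 12 to 25 patients per sub-district (Setting) and the group size of 10 to 20 (CBR delivery), so that a reader can see what ends recruitment.

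The cost is a change of wording and a short calculation. Keeping 334 adds no patients beyond those already stated. Choosing the corrected minimum means 11 more than 264 (12 with equal arms).
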